# 8. STUDY ASSESSMENTS

## **8.1. Safety Assessments**

The safety of this protocol will be assessed by complete physical examination, assessment of hematology and coagulation function, serum chemistry, urinalysis, thyroid function and autoantibody panel.

## **8.2 Clinical response assessments**

All patients who have qualifying measurable disease outside the radiation field according to RECIST criteria, received investigational treatment, had baseline assessments and at least one on-study tumor assessment will be considered evaluable for response. Data on the response of the irradiated lesion will also be collected.

Tumor assessments will be performed at screening/baseline and then at 6-8 weeks following CP-675,206 dosing. Subjects exhibiting stable disease, partial response or complete response at the 8 week timepoint will undergo confirmatory re-evaluation 4-6 weeks following the first documented response. Patients may also be evaluated at 12 weeks following treatment. The same method of assessment and the same techniques used at screening must be performed.

Patients who were treated and removed from the trial prior to on-study tumor assessment for reasons such as patient request, lack of compliance, or as early toxicity (patients who went off study due to serious adverse events related to the trial drug therapy prior to reassessment of tumor lesions) will not be considered evaluable for the secondary objective of efficacy of the trial. Patients who discontinue treatment with stable disease or an unconfirmed response, who subsequently have a response confirmed prior to starting new treatment, will be classified as responders. If no confirmation is obtained, they will be considered as non-responders.

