### **6.1.4. Management of CP-675,206 Toxicity**

CP-675,206 is an immune modulator, so Investigators should be alert for the development of immune-mediated side effects.

The majority of the adverse events reported in early phase trials have been manageable and well tolerated. The most common treatment-emergent, treatment-related adverse event is diarrhea. Diarrhea typically developed 1 to 2 months after the first dose of CP-675,206 (range: 4-72 days).

Although CP-675,206 is a fully human monoclonal antibody, immunogenicity remains a possibility, and thus acute hypersensitivity reactions such as urticaria, pruritus, laryngeal edema, angioedema, bronchospasm, respiratory distress, nausea, vomiting, abdominal cramps and pain, acute back pain, fever, diarrhea, hypotension and fatal anaphylactic shock, as well as sub acute reactions, are also possible. Possible immune-mediated disorders observed involve the skin (vitiligo and cutaneous leukocytoclastic vasculitis), the thyroid gland (autoimmune thyroiditis), the liver (autoimmune hepatitis), the pituitary (hypophysitis) and bone marrow (immune thrombocytopenic purpura). Abnormal lab results that may be immune-mediated include elevations of serum lipase and amylase and liver function tests. There has been one report of treatment-related uveitis, which resolved within 48 hours after treatment with topical steroids. Across all studies, toxicities generally recovered within 12 weeks, allowing continuation of treatment.

If a patient has an adverse event that is thought to be potentially immune-mediated (other than vitiligo), the Investigator should send a blood sample for autoimmune antibody testing.

CP-675,206 is a monoclonal antibody of the IgG2 type, and it is expected that it would cross the placenta if administered to a pregnant woman and could be secreted in breast milk of a lactating woman. The effect of exposure of a fetus or newborn to CP-675,206 is unknown. Women of childbearing potential must agree to use contraception during this trial and for 12 months after the last dose of CP-675,206.

*Note:* In general, it is not expected that the combination of CP-675,206 with this radiation dose will increase CP-675,206-related toxicities. However, radiation of the sites that are the most common autoimmune targets following CP-675,206 administration will be avoided when possible.

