# 10. DATA ANALYSIS/STATISTICAL CONSIDERATIONS

## **10.1. Trial Populations**

The following population will be assessed: An as-treated population, defined as all patients enrolled in the trial that received radiation therapy and one dose of CP-675,206.

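### Section 8.2 drops treated patients without an on-study scan, including those lost to drug toxicity, from efficacy, so any response proportion computed that way runs high

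*Protocol*

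**What the plan says.** Protocol section 8.2 sets the rule in two steps. First, of the treated patients with qualifying measurable disease outside the field, only those who "had baseline assessments and at least one on-study tumor assessment will be considered evaluable for response" enter the response analysis. Second, treated patients "removed from the trial prior to on-study tumor assessment for reasons such as patient request, lack of compliance, or as early toxicity" are said to be outside it, and early toxicity is spelled out as "patients who went off study due to serious adverse events related to the trial drug therapy prior to reassessment of tumor lesions". The consequence is stated broadly: such patients "will not be considered evaluable for the secondary objective of efficacy of the trial".

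The same section fixes the timing: "Tumor assessments will be performed at screening/baseline and then at 6-8 weeks following CP-675,206 dosing". For patients who stop with stable disease or an unconfirmed response, it takes the opposite line to the one it takes for a missing scan: "If no confirmation is obtained, they will be considered as non-responders".

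Section 10.1 names one trial population, "An as-treated population, defined as all patients enrolled in the trial that received radiation therapy and one dose of CP-675,206". Section 10.5.1.1 promises a patient listing of measurability status and best overall response, and section 10.5.1.3 defines PFS from enrollment to progression or death from any cause. Neither repeats the exclusion, and no section counts the excluded patients as non-responders.

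**The concern.** Whether a patient is counted for response depends on something that happens after treatment: staying in the study until a scan at 6 to 8 weeks. The stated reasons include harm from the study drug itself. The list of reasons is open, and the one-scan condition would also catch a patient who dies or deteriorates before imaging without any tumor assessment.

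The loss is plausible here. Section 6.1.4 puts the onset of diarrhea, the most common related event, typically at 1 to 2 months after the first dose, with a range of 4 to 72 days. That overlaps the period before the first scan.

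At stake is the efficacy signal that this phase 1 trial would pass to the planned phase II trial. A proportion among patients who reached a scan answers a narrower question than how many treated patients responded. The PFS data are also affected if the exclusion is read as covering the whole efficacy objective.

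**Working it through.** **The plan's own figure.** Section 10.2 plans at most 6 patients at each of 4 dose levels plus 6 more at the MTD: 4 × 6 + 6 = 30. Adding 2 non-evaluable subjects gives 32. This reproduces. The protocol states no target or expected response rate for this trial, so there is no planned rate to reproduce.

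**Inputs.** Let N be the treated patients with measurable out-of-field disease at baseline, d those among them without an on-study scan, and r the confirmed responses. The documents give none of the three, so the values below are assumptions. An excluded patient has no on-study tumor assessment and so cannot be among the r.

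**Formula.** The rate under section 8.2 is r/(N − d). The rate with everyone kept and missing scans counted as non-response is r/N. Their ratio is N/(N − d), whatever r is, provided r and d are both above zero. With r = 0 both rates are zero.

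| N | d | r | Factor N/(N − d) | Scan-evaluable | All treated, measurable |
|---|---|---|---|---|---|
| 30 | 2 | 3 | 30/28 = 1.07 | 3/28 = 10.7% | 3/30 = 10.0% |
| 24 | 2 | 2 | 24/22 = 1.09 | 2/22 = 9.1% | 2/24 = 8.3% |
| 24 | 6 | 2 | 24/18 = 1.33 | 2/18 = 11.1% | 2/24 = 8.3% |
| 6 | 1 | 1 | 6/5 = 1.20 | 1/5 = 20.0% | 1/6 = 16.7% |
| 6 | 2 | 1 | 6/4 = 1.50 | 1/4 = 25.0% | 1/6 = 16.7% |

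The first row borrows the 2 non-evaluable subjects of section 10.2 only as a scale; that section does not say in what sense they are non-evaluable. Measurable out-of-field disease is not an entry criterion, so N may be smaller than the number treated, and the factor for a given d correspondingly larger.

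**Scale from the earlier multiple-dose study.** Section 2.3.3.3 reports 4/41 and 3/43 responses, while section 2.3.3 gives 44 and 45 patients treated. That is 9.8% against 4/44 = 9.1% (44/41 = 1.07), and 7.0% against 3/45 = 6.7% (45/43 = 1.05). The reason for the smaller denominators is not given, so these show only the order of size.

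**Precision.** Exact 95% intervals at a single dose level are very wide: 1/6 gives 0.4% to 64%, 1/5 gives 0.5% to 72%. Sampling error far exceeds the shift.

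**Response and PFS side by side.** Take a patient who leaves for a drug-related serious adverse event and dies before the first scan. Under section 10.5.1.3 the death is a PFS event. Under section 8.2 the patient is not evaluable for efficacy, and PFS sits among the efficacy analyses of section 10.5.1. The protocol does not say which reading governs.

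**The case against.** The strongest reply is that no stated output or decision depends on this rule. Section 10.5.1.1 plans a listing and no rate, the objective in section 3.2 is only to monitor for evidence of efficacy, and the sample size is empirical with no efficacy test. That stands: the upward shift is conditional on someone forming a proportion, with at least one response and one exclusion.

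Four stronger readings are tempting, and the documents do not support them.

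- *Section 8.2 contradicts section 10.1.* It does not. Section 10.1 does not say that every endpoint uses the whole as-treated population, and section 8.2 defines a subset for one endpoint. The fix below also uses a subset.
- *The phase II dose decision is distorted.* Sections 4.2 and 4.5 rest escalation and the MTD on DLTs and life-threatening events, not on response. If two of six patients left for toxicities that met the DLT definition, section 4.2 would already place that dose above the MTD. Not every drug-related serious event is a DLT, but response enters no stated rule. Nor is a comparison of response by dose planned: section 10.5.2.1 relates immune data to dose and to clinical response.
- *The rule removes almost only failures.* That is inference. Patient request and non-compliance may be unrelated to outcome. Relative to the unknown true rate, the shift would reverse if the excluded would have responded more often than those scanned. What is certain is that none of them can be a documented confirmed responder.
- *Every early leaver is lost.* Section 7.4 requires a final evaluation at discontinuation, and section 8.2.3 accepts clinical examination of superficial lesions, so some early progression could still be recorded.

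It is also fair that the drug is given once, so later toxicity excludes a patient only if the patient leaves the study. That keeps d down.

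None of this removes the rule. The protocol states it outright, so it is not a detail left to an analysis plan, and no other section offsets it.

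**Conclusion.** The point holds in limited form. Section 8.2 excludes treated patients on a post-treatment event, drug toxicity expressly included, and treats a missing scan differently from an unconfirmed response. Any response proportion computed under it would be higher than the all-treated proportion by N/(N − d): about 1.07 for 2 lost of 30, and 1.2 to 1.5 for 1 or 2 lost of 6 at one dose level. These sizes rest on assumed losses and on counting a missing scan as non-response. Whether the excluded patients enter PFS is left open.

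The reach is the descriptive secondary efficacy signal only. The MTD, escalation and safety analyses are untouched, and imprecision at these numbers is larger than the shift. The change is worth making because it is cheap, not because a main conclusion depends on it.

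**What to change.** Amend sections 8.2 and 10.5.1 as follows.

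1. Take as the response denominator all as-treated patients whose baseline assessment shows one or more measurable lesions out of field.
2. List patients without an on-study scan as *not assessed*, with the reason (toxicity, death, clinical progression, withdrawal, non-compliance), and count them as non-responders. This aligns them with the existing treatment of unconfirmed responses.
3. Show the scan-evaluable result as supportive only.
4. State that the exclusion does not apply to PFS, which follows section 10.5.1.3.

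The cost is protocol wording. No new data or visits are needed. The downside is that any response proportion reported may be slightly lower.

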### **8.2.1. Measurability of Tumor Lesions**

Measurements of all lesions should be recorded in metric units. All baseline evaluations must be performed as close as possible to the first day of trial treatment and, in the case of patients with evidence of disease, never more than 4 weeks (28 days) before enrollment. The same method of assessment and the same technique should be used to characterize each identified and reported lesion at baseline and during follow-up.

Measurable Lesions

• If the measurable disease is restricted to a solitary lesion, its neoplastic nature could be confirmed by cytology/histology if necessary.

• Lesions that can be accurately measured in at least 1 dimension (longest diameter to be recorded) as ≥2.0 cm with conventional techniques or ≥1.0 cm with spiral CT scan.

• Clinical lesions will only be considered measurable when they are superficial (eg, skin nodules). Clinically detected lesions will only be considered measurable when they are superficial (eg, skin nodules) and the longest diameter is ≥2 cm. Palpable lymph nodes ≥2.0 cm should be demonstrable by CT scan.

Non-measurable Lesions

• All other lesions, including small lesions (longest diameter <2.0 cm with conventional techniques or <1.0 cm with spiral CT scan) and truly nonmeasurable lesions. Also, skin lesions with longest diameter <1.0 cm and other clinical lesions <2.0 cm. Lesions that are considered nonmeasurable include bone lesions, leptomeningeal disease, ascites, pleural/pericardial effusion, inflammatory breast disease, lymphangitis cutis/pulmonis, and abdominal masses that are not confirmed and followed by imaging techniques. Previously irradiated lesions are nonmeasurable except in cases of documented progression of the lesion since the completion of radiation therapy.

### **8.2.2. “Target” and “Non-Target” Lesions**

Baseline tumor measurements must be performed not more than 4 weeks (28 days) prior to the initiation of treatment with CP-675,206. Patients must have at least one measurable lesion outside of the radiation field at baseline to be included in the analysis of this endpoint. If the measurable disease is restricted to a solitary lesion, its neoplastic nature could be confirmed by cytology/histology if necessary.

Baseline documentation of tumor sites may include imaging assessment of disease in the chest, abdomen and pelvis. A baseline imaging study of the brain is required.

Target Lesions

• Up to 10 total lesions, a maximum of 5 lesions per organ, that are representative of all involved organs may be selected and recorded as target lesions at baseline. Target lesions should be selected on the basis of their size (lesions with the longest diameter) and their suitability for accurate repetitive measurements (either by imaging techniques or clinically). A non-measurable lesion cannot be selected as a target. A sum of the longest diameter (LD) for *all target lesions* will be calculated and reported as the baseline sum LD. The baseline sum LD will be used as reference to further characterize the objective tumor response of the disease.

Non-Target Lesions

• All other lesions (or sites of disease) should be identified as non-target lesions and recorded as non-target lesions at baseline. Measurement of non-target lesions at baseline is not required and should be recorded as “present.” Each non-target lesion should be documented as either present, absent or new in each subsequent evaluation.

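### A measurable lesion that is to be irradiated may be chosen as a target lesion, so local radiation shrinkage can enter the RECIST sum and distort secondary response endpoints

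*Protocol*

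**What the plan says.** Protocol section 8.2 sets who is evaluable for response: "All patients who have qualifying measurable disease outside the radiation field according to RECIST criteria, received investigational treatment", with baseline and at least one on-study tumor assessment. It adds: "Data on the response of the irradiated lesion will also be collected".

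Section 8.2.2 repeats the patient-level condition: "Patients must have at least one measurable lesion outside of the radiation field at baseline to be included in the analysis of this endpoint". It then gives the lesion-level rule. Up to 10 targets, at most 5 per organ, are to represent all involved organs: "Target lesions should be selected on the basis of their size (lesions with the longest diameter) and their suitability for accurate repetitive measurements". The only explicit bar is "A non-measurable lesion cannot be selected as a target". The LD sum is taken over all targets, and every other lesion becomes non-target.

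Section 8.2.1 has one rule about radiation: "Previously irradiated lesions are nonmeasurable except in cases of documented progression of the lesion since the completion of radiation therapy". The same section lists bone lesions as nonmeasurable. On timing it says "All baseline evaluations must be performed as close as possible to the first day of trial treatment", with a limit of 28 days before enrollment.

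Section 8.2.4 defines PR as a fall of at least 30% in the target sum from baseline. PD is a rise of at least 20% from the smallest sum, a new lesion, or unequivocal progression of non-target lesions.

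**The concern.** The scientific aim is regression of disease that was not irradiated (sections 2.1.1 and 2.4.1). Section 2.4.2 expects the radiation dose itself to kill a substantial part of most tumors. The trial has no randomized comparison (section 4.1), and the radiation-only samples in section 8.3 serve the immune assays alone. A response rate therefore cannot be corrected afterwards for local radiation effect by comparison with another group.

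If a lesion in the field sits in the target sum, its shrinkage can be scored as a response to the combination, or can offset growth of out-of-field targets. The classification feeds best overall response (10.5.1.1), response duration (10.5.1.2), PFS (10.5.1.3) and the exploratory link between immune data and clinical response (10.5.2.1). Targets are chosen at baseline by the site, so this rule belongs in the protocol and cannot be left to a later analysis document.

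**Working it through.** **Does any rule keep the irradiated lesion out?**

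- The out-of-field condition in 8.2 and 8.2.2 concerns the patient. A patient with one measurable lesion outside the field and one inside meets it, and both lesions remain open to selection.
- The 8.2.1 rule covers lesions irradiated before they are assessed. Baseline precedes trial radiation, so a lesion awaiting radiation is not yet caught.
- The statement that irradiated-lesion data are also collected suggests separate recording, but does not remove the lesion from the target set.
- The bar on nonmeasurable targets does exclude an irradiated bone lesion. The gap exists only for measurable lesions in the field.

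**Size.** The plan gives no figure to reproduce. The thresholds come from 8.2.4. Lesion sizes and shrinkage below are assumptions, because the protocol gives none.

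Let w be the in-field share of the baseline sum, s the fractional shrinkage of that part, and g the fractional growth of the out-of-field targets.

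Change in sum = −w·s + (1 − w)·g.

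*PR from radiation alone.* With g = 0, PR requires w·s ≥ 0.30, so w ≥ 0.30/s. With g = 0.20, which is PD for the out-of-field targets taken alone, PR requires w ≥ 0.50/(s + 0.20).

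| In-field shrinkage s | Share w for PR, g = 0 | Share w for PR, g = 0.20 |
|---|---|---|
| 50% | 60% | 71.4% |
| 60% | 50% | 62.5% |
| 75% | 40% | 52.6% |
| 100% | 30% | 41.7% |

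*Examples at the first on-study assessment.*

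| In field (cm) | Outside (cm) | Change in sum, all targets | Read as | Out-of-field only | Read as |
|---|---|---|---|---|---|
| 6 → 3 | 4 → 4 | (3 + 4)/10 − 1 = −30% | PR | 0% | SD |
| 6 → 3 | 4 → 4.8 | (3 + 4.8)/10 − 1 = −22% | SD | +20% | PD |
| 5 → 2 | 3 → 3.6 | (2 + 3.6)/8 − 1 = −30% | PR | +20% | PD |
| 5 → 4 | 3 → 3.9 | (4 + 3.9)/8 − 1 = −1.25% | SD | +30% | PD |

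*Masking.* At that assessment the sum reaches PD only if g ≥ (0.20 + w·s)/(1 − w). For 6 cm and 4 cm lesions (w = 0.6) and s = 0.5, this is 0.50/0.40 = 1.25. The outside lesion would have to grow from 4 to 9 cm: (3 + 9)/10 − 1 = +20%.

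Confirmation at 4 weeks or later does not separate the two effects, because it re-reads the same sum.

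**The case against.** The strongest reply is that the out-of-field intent is already on the page. Evaluability rests on disease outside the field, the second statement of that condition stands in the target-lesion section itself, and the irradiated lesion is mentioned as an additional item. That reading of intent is fair: this is a missing exclusion in a selection rule, and the aims do not conflict. It does not tell a site to leave a large measurable in-field lesion off the target list, and the size rule as written allows it.

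Several stronger readings are tempting and are not supported:

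- *That the palliated lesion will usually be a large target.* No lesion sizes are given. Section 2.1.1 names bone as the commonest site of radiation in metastatic disease, and bone lesions cannot be targets. Up to 10 targets across organs would also dilute the in-field share.
- *That response and PFS would simply measure local radiation effect.* New lesions and unequivocal non-target progression are PD whatever the sum. PFS counts deaths. CR needs all lesions to disappear, so in-field shrinkage alone cannot produce it in an evaluable patient. Only growth of out-of-field targets can be masked.
- *That dose-finding is at risk.* Response plays no part in the DLT, escalation or MTD rules (4.2, 4.4, 4.5). Efficacy is secondary (3.2), no response threshold is tested, and about 6–32 patients are expected (10.2).

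**Conclusion.** The gap is real but conditional. As written, section 8.2.2 lets a measurable lesion in the radiation field enter the target sum. Radiation shrinkage alone can then give a PR when w·s ≥ 0.30, or can hold the sum below the PD limit while out-of-field targets grow. The direction is toward more responses and later progression, so best response, response duration, PFS and the immune/clinical correlation can be biased. How often this would happen cannot be derived from the protocol; it depends on how many irradiated lesions are measurable and selected, and on their share and shrinkage. The numerical examples are illustrative and some sit at the PR or PD boundary. The DLT/MTD objective is unaffected. This is a worthwhile, inexpensive correction to secondary endpoints and need not hold up the trial's primary purpose.

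**What to change.** In section 8.2.2, state that target lesions are selected only from measurable lesions outside the radiation field, and that the baseline and follow-up LD sums, and PR and PD by sum, use those lesions alone.

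Put any lesion in the field in a category of its own, neither target nor non-target, and report its response separately and descriptively. Dropping it from the targets is not enough: 8.2.2 makes all remaining lesions non-target, so its persistence would block CR and its unequivocal progression would be PD by default. The text, with 8.2.4 and the table in 8.2.6, should therefore say explicitly whether its persistence counts against CR and whether its progression counts as PD.

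The cost is a few sentences and a field for in- or out-of-field status on the lesion form, with no added imaging. It should be in place before baseline targets are recorded. Non-target lesions need not be measured at baseline, so an out-of-field sum may not be fully recoverable later.
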